##### Timely medical follow-up

Scheduling of colposcopy appointments will be tracked electronically and by exit interview. Timely medical follow-up will be operationalized by whether the patient keeps an appointment for colposcopy within six months of the initial abnormal Pap. Colposcopy is the primary disposition for abnormal Pap tests at EFHS and PAC. Clinic staff endeavor to schedule all patients within three months of the abnormal Pap. Colposcopy is performed on-site at both EFHS and PAC, in order to maximize continuity and follow-up. The procedure may be performed by the patient's primary care physician or by one of several doctors at each clinic who specialize in colposcopy.

##### Patient satisfaction with provider-patient communication

Satisfaction with provider-patient communication will be assessed by the *Doctors Who Communicate Well *scale from the 2.0 Adult Core Survey of the Agency for Healthcare Research and Quality's *Consumer Assessment of Health Plans Study (CAHPS*^®^) [45-47]. The CAHPS scale consists of four items asking the degree to which the provider: listens carefully, explains things understandably, shows respect, and spends enough time with the patient. Each item has 5 response options: never, sometimes, usually, always, I didn't see the provider. The scale's developers recommend collapsing responses to a 3-category distribution by combining "never" and "sometimes" into a single category [48] yielding a 1-3 range per item, where higher numbers indicate better care. Validated in both English and Spanish [45-47], the *Doctors Who Communicate Well *scale shows excellent internal consistency (Chronbach's alpha = .86) and predicts the rated quality of health care [45]. Patients will complete the CAHPS immediately after the follow-up visit for colposcopy.

##### Ancillary outcomes

To support exploratory analyses, patients and providers will be asked several additional questions at the medical follow-up visit.

##### Patient exit interview

After completing the CAHPS, patients will be asked: 1) whether they telephoned the CIS, and if so, how many times; 2) whether any others telephoned the CIS on their behalf, and, if so whom; 3) their satisfaction with the CIS call experience; 4) other ways in which they sought information about screening; 5) whether the doctor who performed the colposcopy was their regular physician; 6) whether family members accompanied them to the visit.

##### Provider exit interview

Because there is, to our knowledge, no existing short scale to measure a patient's skill in communicating with providers, we developed a checklist of patient communication behaviors modeled after the SEGUE Framework [49]. The SEGUE checklist of provider communication tasks is the most widely used tool for physician communication training in North America. The six items to be rated Yes/No are:

No Yes

A) Showed some understanding of Pap/colposcopy

B) Paid attention to what you said

C) Asked 1+ questions

D) Talked about concerns

E) Expressed interest in caring for her health

F) Used time efficiently

*Language barrier and no interpreter

##### Maintenance

Six months after project staff has discontinued the initiative to randomize patients, clinic staff will be interviewed to determine whether either clinic has continued to use the tailored mailing.

### Procedure and data collection

#### Protocol sequence

Clinic staff at both clinics will monitor Pap test results to identify patients eligible for this study. Based on patient flow data, we expect to be able to randomize approximately 100 women from EFHC and 400 women from PAC. Participants will be randomized to two conditions in which they will receive one of two letters previously described: Usual Care participants will receive the general reminder letter about their colposcopy appointment and Intervention participants will receive the reminder letter, plus a request to call the Cancer Information Service ([name]) and suggested questions to ask.

An in-person informed consent process will be undertaken at the colposcopy appointment. Upon arrival for the appointment, clinic staff will remind patients about the letter, inform them about the study, and ask if they are interested in further information. Those interested in further information will be approached by research staff and given a detailed description of the study, emphasizing that participation is completely voluntary. Participants who agree to participate and provide written consent will be enrolled in the study and will receive an exit interview.

#### CIS data collection

Once CIS's usual service is complete, the information specialist will ask the customer service questions in the order listed previously. ECRF will be programmed in such a way that a zip code which falls within the study area will trigger an electronic prompt for the information specialist to ask a series of probing questions. The goal of the probing questions will be to determine if the caller is a part of the study population and if so, from which clinic and which study group (Intervention versus Usual Care). The HFO code will be re-coded to a study code accordingly.

The first probing question is, "Have you or someone you know recently had an appointment at Prentice Ambulatory Clinic or Erie Family Health Center in Chicago? If yes, which clinic?" If the caller responds "no," then a non-study HFO code is used and no more probing questions are asked. If the caller responds either "yes, PAC" or "yes, Erie" the second probing question is asked.

The second probing question is, "Did you or someone you know recently receive a call or letter about having a colposcopy for a positive pap test?" If the answer is "no," then a non-study HFO code is used. If the caller answers, "yes," then the third probing question is asked.

The third probing question is, "Did your letter or telephone call ask you to call [name]?" If the answer is "no," then the call is coded as either PAC Usual Care or EFHS Usual Care, depending on the caller's answer to the first probing question. If the caller answers "yes," then the call is coded as either PAC Intervention or EFHS Intervention, depending on the caller's answer in the first probing question.

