#### Randomization

Patients will be randomized to two conditions that involve different letters from the provider. *Usual Care *participants will receive a generic letter reminding them of their follow-up appointment. *Intervention *participants will receive a targeted letter reminding them of the follow-up appointment, asking them or someone they designate to call CIS, and suggesting some questions to ask.

The patient will be the unit of randomization and the project statistician will prepare and manage the randomization scheme. Separate randomizations will be performed for EFHC and for PAC. Usual Care and Intervention letters will be placed in envelopes. At the time randomization envelopes are selected, group allocation will be concealed from study staff and clinic staff so that there is no selection bias in the randomization process.

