#### Intervention

As soon as the patient has received notification of the lab Pap test result and has been scheduled for a colposcopy appointment, the appropriate control or intervention letter from the provider will be sent, along with a letter informing the patient about the study. The Usual Care letter from the provider will confirm the abnormal Pap and remind the patient of the scheduled follow-up appointment for colposcopy. The Intervention (CIS + Questions) letter from the provider will convey the same appointment information as the Usual Care letter. It will, in addition, ask the patient or a designate to [contact]-CANCER and it will suggest some questions to ask about abnormal Pap tests and colposcopy. The suggested questions are: "What does an abnormal Pap test mean?", "What is colposcopy and what can I expect during colposcopy?", and "How will it benefit me to take the test?"

Consistent with the Institute of Medicine's [42] recommendation, the letters will be appropriate for reading skills at or below an eighth-grade level. The Lexile, a measure of reading difficulty, will be used to gauge reading level [43,44].

Letters will be written in the patient's primary language, Spanish or English. They will be mailed on PAC or EFHC letterhead with a signature per the patient's provider. Text will be typed double-spaced in large font, filling less than a page. Like all materials planned for use in the RCT, the proposed letters will be reviewed with community members and providers during the initial formative phase of the study. The final content of the Usual Care and Intervention letters will be based on input from patients and providers.

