##### Telephone calls to the CIS

The CIS will tabulate calls originating from the study. When CIS information specialists answer the telephone, they log call and caller information into a standard Electronic Call Record Form (ECRF). With the caller's consent, three customer service questions are asked of all callers:

1. Have you used our service before?

2. How did you find our number to call?

3. What is your home ZIP code?

The ECRF response field for Question #2, "How Found Out" (HFO) has many codes, e.g., 300 - TV, 400 - radio, 801- ACS etc., including blank codes that can be assigned to a specific promotion or research study. Four How Found Out response codes will be allocated to identify the conditions in this study: Code 1: PAC, Usual Care; Code 2: PAC, Intervention; Code 3: EFHC, Usual Care; Code 4: EFHC, Intervention.

Information specialists will follow a series of steps (see: ECRF programming below) to determine which, if any, of the four codes should be assigned to a call.

Operationalizing call tracking in this way produces de-identified data. Consequently, it will not be possible to link ECRF-coded call data to the patient's other individual level outcome data. To accomplish such linking, self-reported data on calls to CIS also will be collected from identified participants during the exit interview. This will allow exploratory examination of whether calling the CIS appears to mediate more timely follow-up and improved provider-patient interaction.

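### Study probes launch only on the caller's own home ZIP, so designates living outside the study area get no study code in the CIS tally, a loss that falls mainly on the Intervention arm.

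*Protocol article*

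**What the plan says.** Telephone calls to the CIS: "With the caller's consent, three customer service questions are asked of all callers". The third of these is "What is your home ZIP code", so the ZIP recorded belongs to whoever is calling. The specialists then follow set steps "to determine which, if any, of the four codes should be assigned to a call"; the codes identify clinic and arm.

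CIS data collection sets the entry condition for those steps: "a zip code which falls within the study area will trigger an electronic prompt for the information specialist to ask a series of probing questions". No other trigger is named in the article, which also does not define the study area. The first probe begins "Have you or someone you know recently had an appointment at Prentice Ambulatory Clinic or Erie Family Health Center in Chicago", and the second uses the same you-or-an-acquaintance form.

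Randomization describes the Intervention letter as "asking them or someone they designate to call CIS", and Intervention repeats the invitation to a designate. Usual Care participants "will receive a generic letter reminding them of their follow-up appointment"; no CIS call and no designate is mentioned for them.

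Statistical analysis, Aim 3, defines the measure as whether a study participant calls. It gives 80% power for 5% versus 12% with 250 per group, and more than 99% for the anticipated 5% versus 40%.

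**The concern.** The letter and the probes let a third party call for the patient. The trigger then screens on where that third party lives, which has no bearing on whether the patient is in the trial. A sister in another city who calls at the patient's request is never asked the first probe, although its wording would have included her.

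Only one of the two letters invites such calls, so the loss falls mainly on the Intervention arm. It can shrink the recorded difference on a primary outcome and hide part of the route the intervention is meant to open. The Discussion also reads call counts as a measure of demand, so an understated count matters even when the test is significant. Because the CIS data are de-identified, a call that was not coded cannot be traced to a patient later.

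Callers who decline the ZIP question are missed too, but nothing in the article makes refusal differ by arm.

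**Working it through.** **Inputs from the article.** n = 250 per group; control rate 5%; detectable Intervention rate 12%; anticipated rate 40%; two-sided α = 0.05 (all from Statistical analysis).

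**Inputs not in the article (assumed).** q = share of Intervention calls made by designates; o = share of those designates living outside the study area. Loss L = q × o, with no such loss in Usual Care. Two illustrations:
- q = 25%, o = 25%: L = 6.25%
- q = 40%, o = 50%: L = 20%

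**Formula.** Normal approximation with pooled variance under the null and no continuity correction:
- power = Φ[(d − 1.96·s0)/s1], where d = p2 − p1
- s0 = √[2·p̄(1 − p̄)/250], where p̄ = (p1 + p2)/2
- s1 = √{[p1(1 − p1) + p2(1 − p2)]/250}

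**Step 1: the plan's own figure.** 5% versus 12%: d = 0.070, p̄ = 0.085, s0 = 0.02494, s1 = 0.02475. Then (0.070 − 0.04889)/0.02475 = 0.853, and power is 80.3%. The stated 80% reproduces. For 5% versus 40%, power exceeds 99.9%, also as stated.

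**Step 2: loss in the Intervention arm only.** Recorded rate = true rate × (1 − L).

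| True rate | L | Recorded rate | Recorded difference | Power |
|---|---|---|---|---|
| 12% | 0 | 12% | 7.0 points | 80% |
| 12% | 6.25% | 11.25% | 6.25 points | 73% |
| 12% | 20% | 9.6% | 4.6 points | 51% |
| 40% | 6.25% | 37.5% | 32.5 points | >99% |
| 40% | 20% | 32% | 27 points | >99% |

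**Step 3: ZIP refusal, equal in both arms.** The same proportional loss applies to both rates:
- 10% loss: 4.5% versus 10.8%, power 76%
- 20% loss: 4.0% versus 9.6%, power 70%
- 30% loss: 3.5% versus 8.4%, power 64%

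This costs some power and shrinks the absolute difference, but leaves the ratio of the two rates unchanged.

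**Step 4: the opposite force.** Calls are de-identified, so a patient and her designate who both call can be counted twice. At L = 6.25%, duplicates equal to 1/0.9375 − 1 = 6.7% of the coded Intervention calls would bring 11.25% back to 12%. The net direction of the whole call measure therefore depends on two unknown shares.

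**The case against.** The strongest case against has four parts.

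- **A second measure exists.** The exit interview asks whether others telephoned the CIS on the patient's behalf, with no ZIP condition, and the Discussion says calls are measured by self-report as well as by CIS records. A reader might infer that out-of-area designates are lost to the trial altogether; they are lost only to the CIS tally. But the interview sits under ancillary outcomes, reaches only women who attend and consent, and cannot be linked to the tally. Attendance is itself expected to differ by arm (55% versus 75%). It is a partial remedy.
- **Designate calls may not belong to the outcome.** Aim 3 speaks of a participant calling. On that reading an uncoded relative is not an undercount. The letter and the probes point the other way, so the article is unclear rather than settled. This part stands and needs reconciling.
- **ZIP refusal is not an Intervention problem.** A reader might pool refusers with out-of-area designates and place the whole loss on Intervention. The article gives no ground for that; Step 3 shows the milder effect of an equal loss.
- **The loss may be small.** The study area could be wide. A 30% loss from designates alone would need, for example, 60% of Intervention calls from designates and half of those from outside the area. Nothing in the article supports shares that high, and nothing rules them out.

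**Conclusion.** The mismatch between the ZIP trigger and the invitation to designates is in the text and affects a primary outcome as recorded by the CIS. Taken alone, it biases that comparison toward no effect, because the loss falls mainly on the arm whose letter invites designates.

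The size rests on assumed shares. A 6% to 20% loss of Intervention calls takes 12% to about 11.3% to 9.6%, and power from 80% to about 73% to 51%. If the anticipated 40% is right, power is not threatened and the harm is an understated estimate (37.5% to 32% in the same illustrations).

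A reader might go further and conclude that the reported call effect must be too low. The documents do not support that: double counting pushes the other way, self-report recovers some calls, and it is not settled whether designate calls count.

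**What to change.** 1. Before launch, program the CIS call record to start the probes when the home ZIP is in the study area **or** the call concerns an abnormal Pap test or colposcopy, whatever the ZIP and also when the ZIP is refused. The probes follow the usual service, so the specialist already knows the subject of the call. This condition does not depend on which letter was sent.
2. Do not use a how-found-out answer naming the clinic letter as the added trigger. Of the two provider letters, only the Intervention letter is described as mentioning the CIS. Such a trigger would pick up out-of-area calls better in that arm and could bias the comparison away from no effect.
3. Reconcile Aim 3, which refers to a participant calling, with Randomization, Intervention and CIS data collection: state whether a designate's call counts toward the primary outcome.

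The cost is one added condition in programming that the study needs anyway. The downside is some extra first-probe questions to unrelated callers, who exit at that probe; the article does not give their number.

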### Effective public health communication

From an ecological perspective [9,10], disparities are grounded in a system of reciprocal influences at the intrapersonal, group, community, institutional, and population levels that impede optimal awareness, understanding, decision-making, and action about health. Effective public health communication interventions activate multiple channels to impact the different levels in the ecological framework [11]. Moreover, effective health communication initiatives make their outreach relevant to the intended audience [12]. The need to adopt an audience-centered perspective is especially strong when trying to connect with racial and ethnic minorities. Intrapersonal issues to be considered when making outreach to low-income African Americans and Hispanics include language and attitudinal barriers, low health literacy, lack of information, and misinformation about cancer screening, risk, and treatment [13-16].

Two widely used modes of audience-centric outreach are targeting and tailoring. ***Targeting***, which utilizes a market segmentation approach, creates messages to reach a specific population segment or group, often defined by shared demographics like ethnicity or language. Targeting of physician mailing in the proposed research will be performed on the basis of medical condition, clinic/ethnicity, and language. Of necessity, targeting addresses only surface, observable characteristics [17]. ***Tailoring***, in contrast, creates messages to reach a specific individual whose characteristics are determined by assessment. Because a skilled, non-time-constrained human can tailor messages much more effectively than a computer [18], CIS information specialists highly trained in interpersonal communication will be the tailoring agents for this study.

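### The second CIS screening probe says *positive* Pap test where the letters say *abnormal*, so some true study calls may be coded non-study and a primary outcome undercounted

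*Protocol article*

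**What the plan says.** The section CIS data collection in the Protocol article sets out three probes, asked once the usual service is complete and a study-area ZIP code has triggered a prompt.

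- **Probe 1:** "Have you or someone you know recently had an appointment at Prentice Ambulatory Clinic or Erie Family Health Center in Chicago". On a no, "then a non-study HFO code is used and no more probing questions are asked".
- **Probe 2:** "Did you or someone you know recently receive a call or letter about having a colposcopy for a positive pap test". A no here also gives a non-study code.
- **Probe 3**, reached only after two yes answers, separates Intervention from Usual Care.

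The Intervention section describes the letters: "The Usual Care letter from the provider will confirm the abnormal Pap and remind the patient of the scheduled follow-up appointment for colposcopy". The Intervention letter gives the same appointment information, and "it will suggest some questions to ask about abnormal Pap tests and colposcopy". One suggested question asks what an abnormal Pap test means. The letter text is not settled: "The final content of the Usual Care and Intervention letters will be based on input from patients and providers".

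Among the issues to consider when reaching this population, the section Effective public health communication lists "low health literacy, lack of information, and misinformation about cancer screening, risk, and treatment".

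The section Telephone calls to the CIS says that the coded calls are de-identified and cannot be linked to a patient's other outcomes. Self-reported calls are also collected at the exit interview.

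**The concern.** Probes 1 and 2 together decide whether a call enters the primary count. Probe 2 describes the test result with a word that appears nowhere else in the protocol. A woman, or someone calling for her, who has been told that the Pap test was abnormal may not equate that with a positive test. The section Cervical Cancer Disparities lists being able to report the result correctly as a predictor of good follow-up, so correct reporting cannot be assumed.

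Probe 1 has a smaller weakness. The Intervention letter asks for a call that is to be discussed at the coming colposcopy visit, whereas the probe asks only about an appointment already had.

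A wrong no at either step removes a real study call, and anonymous records leave no way to restore it. The count would understate use of the service. The Discussion also interprets that count as demand for the intervention.

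**Working it through.** **Wording compared**

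| Element | Letters as described | Probe | Match |
|---|---|---|---|
| Communication | letter | call or letter (probe 2) | yes |
| Procedure | colposcopy | colposcopy (probe 2) | yes |
| Result | abnormal | positive (probe 2) | no |
| Visit | scheduled, in the future | recently had (probe 1) | only through an earlier visit |

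For probe 1, eligible women have already had the annual Pap test (Participants), and clinic staff find them by monitoring Pap results (Protocol sequence). Most can therefore say yes on the strength of the Pap visit. A no remains possible in three cases: the caller is thinking of the coming colposcopy; she does not regard the Pap visit as recent (the clinics aim to schedule within three months of the abnormal Pap); or the Pap was done elsewhere. The entry criteria place the colposcopy at the two clinics but do not say outright that the Pap was done there.

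**Inputs** (Statistical analysis): 250 per group, two-sided 5%, call rates of 5% versus 12% for 80% power, and 5% versus 40% as anticipated.

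**Formula** (pooled-variance normal approximation), with p̄ the mean of the two rates:

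power = Φ{ [ |p₂ − p₁| − 1.96·√(2p̄(1−p̄)/n) ] / √([p₁(1−p₁)+p₂(1−p₂)]/n) }

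**The plan's own figure.** For 5% versus 12%, p̄ = 0.085:
- 1.96·√(2×0.085×0.915/250) = 0.0489
- √((0.0475+0.1056)/250) = 0.02475
- (0.07 − 0.0489)/0.02475 = 0.853, so power is 80.3%.

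The stated 80% reproduces. For 5% versus 40%, power exceeds 99.9%, in line with the stated figure of above 99%.

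**Effect of lost calls.** The document gives no loss rate, so let m be an assumed share of true study calls coded non-study, equal in both arms. Each observed rate is the true rate × (1 − m). For m = 0.2, the rates are 4.0% versus 9.6% and p̄ = 0.068:
- 1.96·√(2×0.068×0.932/250) = 0.0441
- √((0.0384+0.0868)/250) = 0.02238
- (0.056 − 0.0441)/0.02238 = 0.53, so power is about 70%.

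| Assumed m | 5% vs 12% becomes | Difference (points) | Power | 5% vs 40% becomes | Difference (points) | Power |
|---|---|---|---|---|---|---|
| 0 | 5.0 vs 12.0 | 7.0 | 80% | 5.0 vs 40.0 | 35.0 | >99.9% |
| 0.1 | 4.5 vs 10.8 | 6.3 | 76% | 4.5 vs 36.0 | 31.5 | >99.9% |
| 0.2 | 4.0 vs 9.6 | 5.6 | 70% | 4.0 vs 32.0 | 28.0 | >99.9% |
| 0.3 | 3.5 vs 8.4 | 4.9 | 64% | 3.5 vs 28.0 | 24.5 | >99.9% |
| 0.5 | 2.5 vs 6.0 | 3.5 | 49% | 2.5 vs 20.0 | 17.5 | >99.9% |

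Under equal loss the ratio of call rates does not change (12/5 = 9.6/4.0 = 2.4), and equal true rates stay equal.

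**The case against.** The case against is substantial, and most of it stands.

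- **Probe 2 has other cues.** It names the letter, the Pap test and the colposcopy, the last being distinctive. It comes after a conversation in which a study caller may just have discussed her abnormal result. This limits the mismatch but does not remove it.
- **The letters are not final.** Nobody can say that the word *positive* will be absent from them. That is a reason to align the script once they are settled.
- **Formative review.** Study sites and phases promises input on all materials for the experimental phase. The CIS script is not among the examples or the focus-group topics, so its inclusion needs confirming, not assuming.
- **A second measure exists.** Self-report at the exit interview does not use the probes. It reaches only women who attend and consent, however, and the Discussion says that neither source can verify the other.

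A reader might infer that a truthful caller must answer no to probe 1 because her colposcopy lies ahead. The text does not support this: the probe asks about any recent clinic appointment, and the Pap visit will usually qualify. A reader might also infer that the test on calls is underpowered. No figure in the plan is wrong, every loss rate above is assumed, and at the anticipated rates power is unaffected even with half the calls lost.

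**Conclusion.** The concern holds as a small, inexpensive improvement to how a primary outcome is measured. The mismatch in probe 2 is plain on the page, and the ambiguity in probe 1 is secondary. The expected effect is an undercount and a smaller absolute difference between letters. A false benefit is not expected, because both arms face the same two probes before probe 3 separates them.

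The size is unknown. At an assumed 20% loss, power falls from about 80% to about 70% if the true rates are 5% and 12%. At the anticipated rates the test is safe, but the estimated difference drops by 7 points, from 35 to 28. These figures rest on equal proportional loss in the two arms, which the document neither states nor contradicts.

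**What to change.** 1. In probe 2, replace *positive* with the term used in the final letters, which on present wording is *abnormal Pap test*. Do the same in Spanish, using the Spanish letter's own words.
2. Let probe 1 cover a past or upcoming appointment at either clinic.
3. Confirm that the probe script is among the materials reviewed in the formative phase.

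These are script edits before launch, with no change to design, sample size or analysis. The one drawback is that a broader probe 1 lets a few more clinic patients from outside the study reach probe 2, which then screens them.

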### Cervical Cancer Disparities

African American women have both increased incidence and the highest rate of mortality from cervical cancer, showing mortality rates more than twice that of non-Hispanic Whites [34]. Survival is also lower among Hispanics, largely because of more advanced cancer at the time of diagnosis [1]. As many as 50% of medically underserved women in the National Breast and Cervical Cancer Early Detection Program failed to receive appropriate follow-up for an abnormal Pap smear, with the likelihood of no follow-up being greatest for African American women [35]. Another recent study of the urban poor found an inadequate follow-up rate of 38%, despite opportunities for follow-up since 86% of women continued to receive care in the same place [36].

Misinformation, lack of information, fear, and embarrassment are all barriers to receiving adequate follow-up care. Predictors of good follow-up are remembering receiving a letter from the provider, knowing the Pap result, being able to report the result correctly, understanding the purpose of colposcopy, having low fear of pain, and feeling confident that the provider will understand the patient's needs [37,38]. Consistent with the health belief model [39], therefore, accurately perceiving one's susceptibility to cervical cancer, feeling confident about being able to take protective action, and perceiving prognostic benefits (versus fatalism) of follow-up for early detection are associated with better follow-up. Telephone outreach addressing these domains has been demonstrated to be effective in increasing follow-up adherence to colposcopy by low-income, inner-city women [40]. An innovation in the proposed research is that telephone support will be provided by CIS information specialists.

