### Experimental phase

#### Study Design

The experimental phase of the study will be conducted using a two-group prospective RCT design comparing the effects of two provider mailing conditions: control (Usual Care) versus intervention (CIS + Questions). The RCT design will be 2 × 2 factorial with Clinic (EFHC versus PAC) and Letter (Usual Care versus Intervention) as between subjects factors.

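### The arms are defined by letters alone, but the call-coding probe also accepts a telephone request as evidence of the Intervention arm, so the two descriptions need to be reconciled

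*Protocol article*

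**What the plan says.** Three sections of the protocol article describe the arms as mailings and nothing else:

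- Study Design speaks of "comparing the effects of two provider mailing conditions: control (Usual Care) versus intervention (CIS + Questions").
- Randomization says "Patients will be randomized to two conditions that involve different letters from the provider".
- Protocol sequence says "Participants will be randomized to two conditions in which they will receive one of two letters previously described".

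The Intervention section gives the contents. Both letters carry the appointment reminder, and only the Intervention letter adds the request that the patient or a designate call the CIS, with sample questions. The letter goes out "As soon as the patient has received notification of the lab Pap test result and has been scheduled for a colposcopy appointment". How the result and the appointment are communicated is not stated.

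The CIS data collection section is wider. The second probe asks "Did you or someone you know recently receive a call or letter about having a colposcopy for a positive pap test". The third begins "The third probing question is, 'Did your letter or telephone call ask you to call"; the name that follows is masked in the text available, but the context is the CIS. A no gives the Usual Care code for the clinic. For a yes, "then the call is coded as either PAC Intervention or EFHS Intervention", whichever route the request took.

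The section on telephone calls to the CIS states that these data are de-identified and cannot be joined to a patient's other outcome data. Aim 3 compares calls by patients as randomized.

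**The concern.** Arm membership for the first primary outcome is taken from what the caller reports having been asked, not from the allocation record. That is tolerable only if what she reports can have come from one arm alone. The telephone wording breaks this condition. A telephone request is not part of either arm as described, yet it earns an Intervention code.

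Contamination of a control group normally dilutes an effect. Under this rule a contaminated Usual Care call would be subtracted from its own arm and added to the other, so along this one pathway contamination would enlarge the apparent effect. Without linkage to the allocation record, nobody could find or reverse the error afterwards.

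**Working it through.** **1. Side-by-side reading.** The request to call the CIS has one described route, the Intervention letter. The third probe recognises two, letter or telephone. Two readings remain:

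- Telephone requests are made. Then the arm definition is incomplete.
- They are not made. Then the probe credits the Intervention arm with an exposure that was not randomized.

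**2. The plan's own figure.** Aim 3 gives 250 per group, 5% versus 12%, 80% power; the article sets a two-sided 5% level. The pooled-variance two-proportion calculation gives 80.3%, so the figure reproduces. For 5% versus 40% power exceeds 99.9%, in line with the stated value above 99%. The sample size is not in question.

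**3. How miscoding enters.** Let pC and pI be the true call rates, f the share of Usual Care calls coded Intervention, and g the share of Intervention calls coded Usual Care. Then

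- observed Usual Care rate = pC(1 − f) + g·pI
- observed Intervention rate = pI(1 − g) + f·pC
- observed difference = (pI − pC) + 2(f·pC − g·pI)

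Neither f nor g is in the documents. All values below are assumptions.

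**4. Telephone pathway alone (g = 0), true rates 5% versus 12%.**

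| f | Usual Care | Intervention | Difference |
|---|---|---|---|
| 0 | 5.0% | 12.0% | 7 points |
| 10% | 4.5% | 12.5% | 8 points |
| 20% | 4.0% | 13.0% | 9 points |
| 50% | 2.5% | 14.5% | 12 points |

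**5. Telephone pathway alone, no true effect.** Two-sided rejection rate of the uncorrected, unstratified two-proportion test, 250 per arm, 400,000 simulated trials per cell:

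| f | 5% in both arms | 12% in both arms |
|---|---|---|
| 0 | 4.9% | 4.9% |
| 5% | 5.6% | 7.0% |
| 10% | 7.9% | 13.3% |
| 20% | 17.5% | 38.0% |
| 30% | 33.5% | 69.7% |

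In counts: 5% of 250 is about 12 callers per arm. Moving four gives 8 versus 16, p = 0.094; moving five gives 7 versus 17, p = 0.036 uncorrected but 0.060 with a continuity correction.

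**6. The opposite error.** An Intervention woman, or her designate, who does not recall the request is coded Usual Care. From the formula the two errors cancel when g = f·pC/pI. At 5% versus 12% and f = 10%, that is g = 10% × 5/12 = 4.2%. At the anticipated 5% versus 40%, it is g = 10% × 5/40 = 1.25%. With f = g = 10% at 5% versus 12%, the difference is 7 + 2(0.5 − 1.2) = 5.6 points, an underestimate. So when the intervention works, a small amount of failed recall outweighs the telephone pathway.

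**The case against.** The strongest reply is that the triggering event is nowhere described. Clinic staff would have to telephone a Usual Care woman and ask her to call the CIS, and she would have to do so. The described procedures imply f = 0, and then nothing happens. A harmless reading also exists: results and appointments may be given by telephone, the second probe allows for that so that eligible callers are not screened out, and the third repeats the phrase. A Usual Care woman who had only a routine call would truthfully answer no and be coded correctly. A journal article also need not set out every clinic contact. Finally, calls are collected by self-report at the exit interview as well, from identified participants whose arm need not come from this probe.

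Most of this stands. It removes any claim about frequency, and silence on routine telephone contact is not itself a fault. It does not remove the mismatch, because the article states the coding algorithm in full and that algorithm does not fit its own arm definition. Self-report covers only women who attend and consent, and the Discussion acknowledges that it cannot verify the CIS log.

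Two stronger readings are tempting. A reader might infer that the rule biases the call comparison in favour of the intervention. The documents do not support this, because recall errors run the other way and neither rate is given. A reader might also infer that unequal telephone contact distorts the colposcopy outcome, since the Background says "Telephone outreach addressing these domains has been demonstrated to be effective in increasing follow-up adherence to colposcopy by low-income, inner-city women". But that sentence concerns outreach on beliefs, fear and understanding, and nothing suggests that telephone contact differs between arms.

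**Conclusion.** The point holds as an internal mismatch in the coding rule for the first primary outcome: the third probe is wider than the randomized treatment, or the treatment is incompletely described. Its consequence is conditional. Each Usual Care call prompted by telephone would widen the observed gap by two calls, one lost and one gained, with no means of correction. The number of such calls is unknown and may be zero. The net direction across all coding errors is not fixed, and no effect on colposcopy attendance is shown. Against the anticipated 5% versus 40%, a few stray codes matter little; near 5% versus 12%, or with no true effect, they could matter. This is a cheap improvement to make before calls are logged, not a demonstrated bias.

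**What to change.** Reconcile the Intervention and CIS data collection sections.

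- **If the request is made by letter only:** restrict the third probe to the letter. Give telephone-only prompts a separate spare How Found Out code, report them separately, and add a sensitivity analysis that counts them in either arm. State that clinic telephone contact about the appointment is the same in both arms and does not mention the CIS.
- **If telephone requests are part of the Intervention:** say so in the arm definition.
- **Preferably, in either case:** print a neutral code in both letters and have the information specialist ask for it, so that arm comes from allocation instead of recall. This also addresses the opposite error, which rewording the probe does not.

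The cost is one reworded probe, one more code from a field that already has blank codes for research use, and a one-line instruction to clinic staff; the letter code adds a line to each letter. The downside is that a few Intervention callers who remember only a telephone call leave the main count. Sample size and test are unchanged.
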